
### Process evaluation

In line with the MRC guidance on process evaluations, this study will include a process evaluation that is appropriate for the feasibility testing stage of the development-evaluation-implementation process for this intervention [52]. This process evaluation will allow for the exploration of the feasibility of implementation of the intervention by assessing uptake (recruitment) and retention, participant engagement, fidelity of delivery (to content and quality), experiences of participants and facilitators, unintended consequences, and contextual factors which may influence experience and delivery.

The following data collection tools will be used to assess fidelity of intervention delivery, participant and trainer characteristics/motivations, trainer knowledge and self-efficacy to deliver the programme, participant engagement with the programme/online materials, and acceptability of the intervention and trial design.
Facilitator pre-training questionnaire: We will use a pre-training questionnaire to collect information about facilitators’ characteristics, their motivations to take part, relevant background and experience, and expectations of delivering the programme.Facilitator training feedback: Following delivery of the training, we will use a questionnaire to gather the facilitators’ feedback about their self-reported knowledge, understanding, skills, and confidence to deliver the intervention and to gather their reflections on the training.Facilitator delivery observations: We will use a checklist to assess lead facilitators’ competence to deliver while observing their delivery of the programme content during the facilitator training. The checklist includes key skills and competencies linking to the objectives of the lead facilitator training and will enable trainers and research staff to assess facilitators’ readiness to deliver the programme. This will also help to guide and plan additional or future training.Facilitator checklist, records, and support calls: We will use a self-report checklist completed jointly by the facilitators to indicate which content they have covered in each session (adherence), the duration of the sessions (dose), and the participants’ engagement. Facilitators will be asked to record attendance at each session. We will also arrange support calls with facilitators to gather more information about how the groups are going and any challenges to delivery.Session recordings: We will audio-record group sessions and will sample two to three recordings from each group to assess fidelity to intervention content, quality of delivery, and participant engagement. A researcher will rate the delivery using the same checklist used by the facilitators after each session. A second researcher will rate one recording per group (*n* = 6, 14%). The two researchers will compare the scoring of the first three groups immediately, and any inconsistencies will be discussed with [name], to ensure there is a clear understanding of the assessment criteria. The scores of the double-coded sessions will be agreed between researchers, and the sessions assessed by the researchers will be compared with the facilitators’ scores.Participants’ feedback: We will collect feedback from treatment and control arm participants about the programme content and delivery, their experiences, and whether they had contact with participants in the other arm of the trial via feedback forms at the end of each group session for those in the intervention arm and at the end of the programme for those in both trial arms.Participant interviews: We will sample purposively 12 participants (from different groups) in the intervention arm and 6 participants allocated to the control arm across all sites for semi-structured telephone interviews. For the intervention arm, these interviews will explore participants’ experiences of, and engagement in, the programme and the group and their views on the group content, activities, and facilitators. All, control and intervention groups, participants will be asked in the interviews about engagement with online resources, perceived impact of the programme and any potential contextual influences, and acceptability of the trial processes and measures. We will also sample up to 4 participants (from different groups) who were allocated to the intervention arm of the trial but did not attend any group sessions to ask them about barriers to attending and whether anything could be done to promote attendance in future groups. All interviews with participants will last approximately 30 min and will be audio-recorded and transcribed verbatim, with names and other personal identifying information changed to protect confidentiality. Interviews will take place as soon as possible after the participants have completed their post-intervention measures and before they complete their 6-month follow-up measures.Focus groups with facilitators: We will invite all lead facilitators and assistant facilitators to a focus group after the end of all groups. The focus group (lasting approximately 2 h) will cover facilitators’ experiences of delivering, and engagement with, the programme, views on the programme content, activities and feasibility of programme delivery, facilitator training and skills, group management, and suggestions for improvements. The focus group will be audio-recorded and transcribed verbatim (with any potentially identifiable information anonymised).

### Cost-effectiveness framework

We will develop and test a framework for assessing the cost-effectiveness of the intervention in a future randomised trial. We will:
Establish methods for estimating intervention resource use and costs (e.g. training of facilitators, facilitators’ time, venue hire), in collaboration with the programme facilitators and site representativesDevelop a resource use questionnaire in collaboration with parent carers, drawing on measures in the Database of Instruments for Resource Use Measurement (DIRUM) repository [51]Assess the acceptability to parent carers of the EQ-5D-5 L, the ICECAP-A, and the WEMWBS, judged by missing data and measurement properties [53].

### Data analysis

#### Statistical/quantitative analysis

We will report the number of eligible people who self-refer and the percentage (with 95% confidence intervals (CIs)) of these that are randomised in the trial. These findings will also be reported separately for each type of delivery setting and delivery model to assess whether particular delivery settings or models are more popular and therefore would lead to higher recruitment rates in the subsequent definitive trial. We will also report numbers and percentages of people who heard about the study via different sources, organised into categories.

We will also report the percentage (with 95% confidence intervals) of participants who complete each assessment at each time point as an assessment of the acceptability of the measures and of the feasibility of collecting sufficient data in a definitive trial. We will summarise the characteristics of recruited participants using demographic data to allow for assessment of the representativeness of the sample relative to figures available from the Office for National Statistics on the population in the southwest of England. We will also report the baseline comparability of the trial arms with respect to demographics and outcome measures.

For the intervention arm, we will report the number and percentage of participants that attend each group session with 95% confidence intervals. The percentage of participants that are lost to follow-up at each follow-up point will be reported for each trial arm. Select characteristics (parent carer gender and age, child gender and age, Index of Multiple Deprivation quintile, study site (centre), and baseline scores on outcomes) will be compared between those who are and are not lost to follow-up within each trial arm using descriptive summaries, but no formal statistical tests. Acceptability, judged by missing data of EQ-5D-5 L and ICECAP-A, will help to plan methods for estimation of cost-effectiveness in the future trial.

Means, standard deviations, and the correlation between baseline and follow-up scores on continuous outcomes will be reported to inform the sample size calculation for the subsequent definitive trial.

Level of clustering within groups in the intervention arm will be quantified using the intra-cluster (intra-group) correlation coefficient to inform the sample size calculation for the definitive trial; however, we recognise the relatively small sample size for this purpose, and it will be used alongside information about levels of clustering in published studies of trials of similar group-based interventions in similar settings.

We will compare the outcomes at follow-up between the two trial arms based on the intention-to-treat principle with participants analysed according to the trial arm they were randomised to. Missing data will not be imputed. We will report only confidence intervals for the intervention effect and no *p* values, in line with the extension to the CONSORT statement for reporting randomised pilot and feasibility studies [54].

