### Inclusion criteria

People meeting the inclusion criteria are (1) primary carers of children with additional needs and/or disabilities (participants who self-identify as primary carers are eligible; the child can be up to 25 years old consistent with the current Department of Health and Department of Education Special Educational Needs and Disability (SEND) legislation in England and The Children’s Act; no named diagnosis is necessary, and we are not limiting to specific conditions), (2) willing and able to attend the programme group meeting session(s) on arranged dates/times, and (3) able to access online information.

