### Intervention

The group-based programme was developed using Intervention Mapping approach [28]. Full details of the intervention, including its development, logic model, and content (e.g. activities, behaviour change techniques), are available in a previous publication [29]. In brief, the programme aims to expand parent carers’ social networks and provide social support from peers with a shared sense of social identity alongside targeted activities to improve parent carers’ confidence, motivation, self-efficacy, and empowerment, thus creating the conditions for change necessary for them to feel able to make their own plan to prioritise healthy behaviours for themselves.

The programme content is based around a set of universal and evidence-based actions (called CLANGERS) associated with health and well-being. CLANGERS stands for Connect, Learn, be Active, Notice, Give, Eat well, Relax and Sleep [31]. The ‘CLANG’ component comprises the ‘Five Ways to Wellbeing’ based on the evidence from the foresight project on Mental Capital and Wellbeing [32]. Each of these behaviours is potentially more difficult for parent carers.

The programme content is organised into 12 modules lasting 2 h each. The modules can be delivered weekly over 6 sessions (comprising 2 modules per session) or 12 sessions (1 module per session). Our Family Faculty PPI working group suggested that offering either 6 longer sessions in the daytime or 12 shorter evening sessions would be reasonable for most parent carers. One or both options will be offered per area in order to maximise recruitment and to reflect likely real-world delivery in community settings, with 6 groups being delivered in the study in total. If uptake is very low for a particular site, the delivery model may be adapted during recruitment to increase numbers.

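### The recruitment percentage by delivery model counts only people whom the model's timing already suits, so on its own it can miss or reverse a difference in popularity

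*Protocol article*

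**What the plan says.** Under Statistical/quantitative analysis, the article will report the "number of eligible people who self-refer and the percentage (with 95% confidence intervals (CIs)) of these that are randomised". These results will also be "reported separately for each type of delivery setting and delivery model to assess whether particular delivery settings or models are more popular". The same sentence draws a forecast from the breakdown, namely whether some "models are more popular and therefore would lead to higher recruitment rates in the subsequent definitive trial".

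Under Inclusion criteria, the second criterion is being "willing and able to attend the programme group meeting session(s) on arranged dates/times". The other criteria are being a primary carer and having online access; not being able to communicate in English is the exclusion.

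Under Intervention, the models differ in timing and length: the parent working group advised that "offering either 6 longer sessions in the daytime or 12 shorter evening sessions would be reasonable for most parent carers". Models are not assigned by design: "One or both options will be offered per area in order to maximise recruitment". They can also change: "If uptake is very low for a particular site, the delivery model may be adapted during recruitment to increase numbers".

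Under Allocation to trial arms, each of the six groups is a site, and those randomised there are the people who chose that group. Under Study records, the team will log advert responders, reasons for not taking part among decliners, setting, model, and time to reach target at each site.

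**The concern.** A model's popularity shows first in how many interested carers can and will come at its times. The second inclusion criterion settles that question before anyone enters the denominator. What remains is the step from eligible to randomised, which mainly reflects willingness to consent and be randomised. The link is direct for the delivery model. For the setting it holds to the extent that being able to attend includes reaching the venue.

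The article draws a forecast from this breakdown: the more popular models are expected to recruit better in the definitive trial. If the percentage is read that way, the later trial could adopt a format that converts well among the few it suits over one that would recruit more carers from the same pool of interest.

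**Working it through.** The plan states no recruitment figure by model, so there is none to reproduce. The check is on what the percentage depends on.

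**Definitions.** For a given model, among enquirers who meet all the other criteria:

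- *a* = share who can and will attend at the arranged times (second inclusion criterion)
- *c* = share of those who are then randomised

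Planned percentage = randomised / eligible = *c*. 
Recruitment per enquirer = randomised / all such enquirers = *a* × *c*.

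The planned percentage does not contain *a*, the quantity in which a daytime and an evening format would be expected to differ.

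**Illustration.** All inputs are assumptions: 100 enquirers per model, labelled A and B. Intervals are Wilson 95%.

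| Case | *a*: A, B | *c*: A, B | Eligible: A, B | Randomised: A, B | Planned %: A, B | Per enquirer %: A, B |
|---|---|---|---|---|---|---|
| 1 | 60%, 30% | 80%, 80% | 60, 30 | 48, 24 | 80 (68–88), 80 (63–91) | 48 (38–58), 24 (17–33) |
| 2 | 70%, 50% | 80%, 80% | 70, 50 | 56, 40 | 80 (69–88), 80 (67–89) | 56 (46–65), 40 (31–50) |
| 3 | 60%, 30% | 70%, 90% | 60, 30 | 42, 27 | 70 (57–80), 90 (74–97) | 42 (33–52), 27 (19–36) |

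- Case 1: a two-fold difference (48/24 = 2) does not appear in the planned percentage.
- Case 2: a smaller difference (56/40 = 1.4) does not appear either.
- Case 3: the planned percentage favours B, yet A recruits more per enquirer (42/27 = 1.56).

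In general the order reverses when *c*(A) < *c*(B) but *a*(A)/*a*(B) > *c*(B)/*c*(A). In case 3, 60/30 = 2 exceeds 90/70 = 1.29.

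**Do the counts repair this?** The number eligible is also reported by model, and in case 1 it shows 60 against 30. That works only because both models were given 100 enquirers. Halve A's enquirers to 50 and keep B's at 100. A then has 50 × 0.6 = 30 eligible and 30 × 0.8 = 24 randomised; B has 100 × 0.3 = 30 and 30 × 0.8 = 24. Counts and percentages now agree exactly, while recruitment per enquirer is still 24/50 = 48% against 24/100 = 24%. Without the number of enquirers offered each model, the counts do not give relative popularity.

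**The case against.** The best defence is that the percentage is not the only thing reported. Counts of eligible people by model are planned too, and the records include advert responders, reasons for declining and accrual time per site. Accrual time bears on recruitment by model and does not depend on the eligibility denominator. This stands, and it limits the point: it is too much to say that the trial could not show which model is more popular. What remains is that the analysis section ties the popularity reading to the counts and percentage of eligible people, and does not use the other records for it.

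Three further readings are tempting and not supported:

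- *That everyone put off by one model is lost.* Where both options are offered in an area, a carer who cannot attend one may qualify through the other.
- *That after a switch of model, earlier refusals are counted under the replacement.* The article allows the switch but does not say how earlier enquirers are classified, and such a rule may stand in the full protocol or analysis plan.
- *That the 14% of recordings to be double-rated (six) reveals five six-session groups and one twelve-session group.* Six of 42 sessions is 14.3%, but six of 43 (14.0%) and six of 44 (13.6%) also round to 14%. Two twelve-session groups would give 4 × 6 + 2 × 12 = 48 sessions, and with four to six unrecorded they fit as well.

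It is also fair that the alternative denominator is imperfect, since enquirer numbers reflect local publicity. Finally, popularity by model is neither a listed objective nor one of the three feasibility indicators in the Discussion.

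**Conclusion.** The point holds in limited form. The percentage by setting and model is conditional on the feature that distinguishes the models, so on its own it can hide a difference in popularity or reverse it; the counts of eligible people help only in part. This follows from the stated denominator and the inclusion criterion and needs no assumed numbers. The sizes shown (80% against 80% masking 48% against 24%; 70% against 90% reversing 42% against 27%) rest wholly on assumed attendance and conversion rates and are not predictions.

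With six groups, each its own site, and models not assigned by design, model is also confounded with site. Any comparison by model is descriptive, whichever denominator is used.

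The consequence is confined to advice on format for the definitive trial. The progression decision and the outcome analyses are unaffected.

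**What to change.** 1. For the comparison by setting and model, take as denominator all self-referrers who meet the other criteria (primary carer, able to communicate in English, online access).
2. Report inability to attend at the arranged times as an outcome in that table, beside declined and randomised.
3. Classify each person by the model or models offered at first contact. If a site's model is later adapted because uptake is low, its earlier refusals then stay with the original offer.
4. Show the results by site and label them descriptive.
5. Keep the eligible-to-randomised percentage as the overall measure of the acceptability of randomisation.

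The cost is small: one reason code and a field for the date and model offered in the screening records, then re-tabulation. The planned reasons cover those who decline, so people screened out on timing need the explicit code. If recruitment has closed, use what the log holds and show enquirers without a recorded reason as a separate row. The downsides are that recruitment percentages will look lower, and that differences in enquirer numbers between sites will partly reflect local publicity, which should be said beside the table.

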#### Analysis of process data

Descriptive statistics will be reported for the quantitative data collected in delivery observation checklists, facilitator checklists, checklists used to assess intervention session recordings, and participant feedback forms.

Qualitative data collected from feedback forms, interviews, and focus groups will be analysed thematically to provide insights into participants’ experiences of the programme, intervention acceptability, and suggestions for improvement, and to enhance understanding of the impact of the intervention and the mechanisms of change in relation to the programme logic model [54]. Data will be analysed using inductive thematic analysis [55] separately for each data source (i.e. feedback comments, interviews, and focus groups), following the same approach. Some issues will emerge as more salient than others and the interpretation of findings will be influenced by the original research objectives as well as the themes emerging directly from the data.

NVivo software (version 12 Pro for Windows, QSR International) will be used to organise and analyse the qualitative data. Initially, two researchers will independently read and code line-by-line a sample of the data and discuss their coding to develop and agree on the coding framework. New codes may be added as the coding proceeds, and the codes and coded data will be reviewed. Codes will be defined, compared to each other, and organised into categories and themes. Attention will be paid to negative, or ‘deviant’, cases to inform developing themes and interpretation. Short summaries of each interview will be also written to explore how individual experiences and views of the intervention may differ between participants. The analysis and interpretation of the data will be regularly discussed with the research team. A detailed record will be kept of the analysis process, including definitions of the themes and concepts and their application.

## Discussion

We will interpret the findings of this feasibility trial and report the implications for progression to a definitive randomised controlled trial of the HPC programme. This will include any necessary amendments to the intervention content and delivery, as well as the development of a train-the-trainer manual to be used in training future facilitators of the programme. The following indicators of feasibility will be used to determine whether a definitive randomised controlled trial is feasible with the current trial design and procedures:
Recruit a minimum of 48 participants, which is the minimum number that will enable all six sites to be randomised and the intervention to be testedDeliver 6 groups in total for the intervention arm, assessed by establishing 6 venues, and identifying and training facilitators, and groups completing the programme curriculumAt least 80% of participants completing measures at 6-month follow-up or a clear plan to achieve this in the trial

If any of these indicators are not met, the research team will consider whether a definitive trial may not be feasible or whether changes to the design or procedures and further feasibility testing are needed. The need to translate programme materials into other languages will also be taken into account for a subsequent trial.

A complete and transparent report of the trial will be produced with reference to recommendations of the CONSORT 2010 statement: extension to randomised pilot and feasibility trials, including a CONSORT participant flow chart [54]. The report will be written for publication in a peer-reviewed, open access, academic journal with authorship eligibility determined by following the International Committee of Medical Journal Editors recommendations [56]. A plain language summary of the findings will also be co-produced with members of our Family Faculty public involvement group and sent to trial participants and organisations that help to recruit participants and host the groups. We will consult our Family Faculty and Stakeholder Advisory Group for advice on ways to disseminate the findings.

NHS England’s Commitment to Carers states ‘Helping carers to provide better care and to stay well themselves will contribute to better lives for those needing care and more effective use of NHS resources’ [57]. However, there is currently a paucity of interventions that promote health for parent carers. This feasibility trial and a subsequent definitive trial may have important implications for a public health strategy for parent carers of children with disabilities in the UK. It will also inform research and public health policy internationally, as the higher risk of psychological and physical health problems in parent carers is not limited to the UK.

